**Fig. 1 Fig1:**
[figure not shown]
Schedule of study procedures. Abbreviations: *FBT* family-based treatment, *FBT-HT* home treatment as an add-on to FBT, *FBT-MBSR* home treatment as an add-on to a mindfulness-based stress reduction program, *HT* home treatment

### Interventions

Professionals providing FBT in the three treatment groups will follow the FBT manual [26] and will be trained during a 2-day introductory course in FBT for AN offered by the Training Institute for Child and Adolescent Eating Disorders and led by [name] and [name]. All study participants will receive a weekly FBT session with a trained FBT clinician. In addition, the FBT-HT group will receive two 60–90-min consultations per week at home, conducted by a qualified FBT-HT professional. The FBT-MBSR group will receive two 60–90-min consultations delivered by a qualified MBSR trainer. FBT-HT professionals are to be graduate nurses or social workers with graduate professional degrees and experience in inpatient and outpatient treatment of adolescent eating disorders. The concept of milieu therapy appears against the background of an interdisciplinary understanding as a holistic treatment approach for children and adolescents with psychiatric disorders [18]. Milieu therapy is delivered by nurses and/or social workers and therefore requires fewer psychotherapeutic resources and is less costly. The relational style of milieu therapists differs from that of psychotherapists, it is predominantly daily, very action-oriented and less detached. The MBSR trainers are to be psychologists with a master’s degree who have completed a one-semester workshop on MBSR at the University of Zurich. FBT-HT professionals are to be trained in FBT treatment of adolescents with eating disorders through a workshop and ongoing group supervision by a clinical psychologist with a master’s degree and specific experience with AN. All professionals providing FBT will receive weekly supervision by a psychologist holding a master’s degree or a doctoral degree as part of the standard organizational procedure.

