Outreach services generally offer greater flexibility in terms of time and location, enabling the support of family structures in their ordinary environment, which minimizes the burden on all family members [6]. Such services are generally used to intensify treatment during a severe course of illness [24] and, in treatment for eating disorders, to prevent inpatient hospital admissions [30]. Transferring treatment strategies to the home setting is the key challenge to achieving sustained symptom reversal and long-term success in childhood and adolescent mental health treatment [36]. Specifically for adolescents with eating disorders, incorporating home treatment (HT) has been shown to be feasible and acceptable [9, 17], with a significant increase in treatment effects [30]. FBT is particularly well suited as a supplement to HT because the specific eating situations observed in FBT as possible maintaining factors [10] require effective management in the home setting. A recent qualitative study examined parents’ experiences and perceived stress in the context of FBT treatment and symptom persistence in their child [37]. HT could be a supportive element to reassure parents in their tasks prescribed in the FBT sessions and help the family to (re-)establish more beneficial and supportive interactions.

As postulated by Omer and London [29], the therapeutic relationship is the most important factor for therapeutic success. Although several HT programs for adolescents with psychiatric disorders have been developed and evaluated as effective [2, 24], to date, no studies have been able to demonstrate that the greater effectiveness of home-based care was not simply owing to the more intense therapeutic relationship, which may result from the additional time spent with the patient or the greater intimacy of the therapy environment.

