#### FBT: MBSR (control group)

During the 12-week treatment period, FBT-MBSR is to include two 30-min consultations per week to practice and implement mindfulness for patients. The MBSR interventions are manualized exercises and meditations based on the 8-week MBSR program described by Kabat-Zinn [21]. The exercises and meditations are adapted to the needs of adolescents and supplemented with practices from mindfulness exercises with children and adolescents in psychotherapy [13]. To not to deviate further from the 8-week program manual, MBSR sessions are not timed to coincide with HT sessions. To support standardization and daily practice, meditation podcasts are provided, each lasting between 6 and 13 min. The MBSR therapist makes home visits for sessions or offers online appointments upon request. Each session includes meditation, a mindfulness exercise and also an opportunity to share and receive answers to possible questions.

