### Power analysis

The target sample size for the primary analysis was derived from an a priori power calculation using G*Power (version 3.1.9.7) and repeated measures ANOVA as a statistical model. Assuming a small effect size of *f* = 0.2, power of 80%, type 1 error level of *p* < 0.05 and correlation among repeated measures of *r* = 0.5, the necessary total sample size of 66 is adequate to test our main hypothesis involving three groups, two time points and the statistical interaction term. Assuming a reasonable attrition rate of 25%, we set our target sample to 90, equivalent to 30 participants per group, assuming equal treatment arm sizes. This number also aligns with the study feasibility, as it approximates the number of eligible patients who previously registered at the outpatient clinic over time intervals similar to the planned recruitment period of 3 years.

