### Data analysis plan

The initial descriptive statistics will summarize participant data characteristics as means, standard deviations, minima, maxima, frequencies and percentages. The validity of stratified randomization will be evaluated by inspecting between-group differences at baseline by means of a one-way analysis of variance (ANOVA), Kruskall–Wallis test or chi-squared test (in dependency of conventional statistical assumptions and the variable type, i.e., continuous versus categorical). Outcome data will be evaluated for the normality assumption by a combination of visual (Q–Q plots, histograms) and statistical (Shapiro–Wilk test) methods and will be transformed if necessary to meet the normality assumption. Participant characteristics of the analyzed sample and dropouts will be subjected to an additional inspection for possible non-random differences. Missing data will be handled by the maximum likelihood estimation method. The effects of the interventions will be assessed as changes in the primary outcomes from pre-test to post-test and follow-up assessment using EDE, EDI-2 and BMI analyzed with a repeated measures ANOVA followed by a post-hoc Tukey’s test to compare treatment means when there is a significant effect. The potential influence of confounding factors (age, premorbid BMI, duration of illness, age at onset, duration and setting of pre-treatment, medication use) will be further explored in sensitivity analyses. The secondary continuous variables will be analyzed in parallel. The measures related to treatment implementation (FBB, BPT) will be evaluated using descriptive statistics. Corrected effect sizes, expressed as Hedges’s *g* and significant deviations beyond the 95% confidence interval, will be computed for between- and within-group terms and will indicate empirical power estimates for a subsequent confirmatory study. Exploratory analyses will test the FB-K measure as a mediator/moderator of efficacy. To examine the FBT process, the ratings of each therapy session by the adolescents and the therapists will be compared and analyzed to assess their common development over time. More advanced statistical methods, such as generalized estimating equations (GEE) (which allow for more flexible modelling of the correlation structure among observations, are less sensitive to violation of assumptions and estimate population-wide average effects) will be also applied to assess differences in BMI percentiles and EDE/EDI-2 trajectories. The statistical significance threshold will be set to *p* < 0.05.

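### Add-on providers are nested within arm, but the planned ANOVA and the sample size treat patients as independent; a provider-clustered sensitivity analysis should be pre-specified

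*Protocol article*

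**What the plan says.** **Delivery.** Under Interventions, all three arms receive weekly FBT from a trained clinician. In addition, "the FBT-HT group will receive two 60–90-min consultations per week at home, conducted by a qualified FBT-HT professional". These professionals are nurses or social workers. The second add-on is delivered by master's-level psychologists trained in MBSR; the section on the MBSR control group adds: "The MBSR therapist makes home visits for sessions or offers online appointments upon request". The FBT arm has no add-on provider. Add-on staff therefore belong to one arm by role and profession. No number of providers or caseload is stated.

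**Analysis.** The Data analysis plan assesses change in the primary outcomes "using EDE, EDI-2 and BMI analyzed with a repeated measures ANOVA", with Tukey comparisons after a significant effect, and adds: "The statistical significance threshold will be set to *p* < 0.05". Provider is not among the factors listed for sensitivity analyses. GEE is named as an additional method for trajectories, without a provider cluster.

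**Sample size.** The Power analysis reads "Assuming a small effect size of *f* = 0.2, power of 80%, type 1 error level of *p* < 0.05", with "correlation among repeated measures of *r* = 0.5". This gives 66 patients, raised to 90 (30 per arm) for 25% attrition. The only correlation considered is that between a patient's own repeated measurements. There is no design effect.

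**The concern.** A repeated measures ANOVA with only person-level error assumes that two patients in the same arm are no more alike because the same person treated them. Here the add-on involves two contacts a week for 12 weeks with an individual professional, and that professional works in one arm only. Differences between individual providers then move the arm mean, while the error term reflects little of them. The test asks whether these treatments with these providers differ, but the result will be read as a comparison of HT with MBSR or with FBT alone.

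At stake are the standard errors of three contrasts. HT versus MBSR is affected in both arms. HT versus FBT and MBSR versus FBT are each affected in one arm. The sample size carries the same assumption, so the power of a correctly calibrated comparison is lower than stated.

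**Working it through.** **1. The plan's own figure.** For the group-by-time interaction with k = 3 groups, m = 2 time points, f = 0.2 and r = 0.5:

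λ = f²·N·m/(1 − r), df₁ = (k − 1)(m − 1) = 2, df₂ = (N − k)(m − 1).

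For N = 66, λ = 0.04 × 66 × 2/0.5 = 10.56 and df₂ = 63, giving power 0.818. N = 63 gives 0.798 and N = 64 gives 0.805. So 66 is the smallest multiple of three that reaches 80%. For attrition, 66/0.75 = 88, and 90 is consistent. The figure reproduces for independent patients.

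**2. What shared providers do.** With two time points the interaction test is a one-way F test on change scores. Assume c equally loaded providers per add-on arm and an ICC ρ for the change score. The variance of an add-on arm's mean is multiplied by 1 + (n/c − 1)ρ.

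Hand check with n = 30, c = 3, ρ = 0.05:
- Design effect: 1 + (10 − 1) × 0.05 = 1.45, so the arm mean has variance 1.45/30 = 0.0483 in units of the patient variance.
- Expected within-arm sample variance: (30/29) × (1 − 0.0483) = 0.984.
- The standard error of HT versus MBSR is too small by a factor √(1.45/0.984) = 1.21.
- The nominal critical value of 2.00 (58 df) acts as 2.00/1.21 ≈ 1.65, a two-sided error of about 10%.

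**3. Simulated omnibus rejection, no treatment effect.** 40,000 trials per cell, nominal 5%, provider effects in the two add-on arms only. **Both c and ρ are assumptions.**

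| Patients per arm | ICC | c = 2 | c = 3 | c = 4 | c = 6 | c = 10 |
|---|---|---|---|---|---|---|
| 30 | 0.02 | 7.9% | 6.8% | 6.3% | 5.7% | 5.4% |
| 30 | 0.05 | 13.2% | 10.3% | 8.5% | 7.2% | 5.9% |
| 30 | 0.10 | 21.4% | 15.4% | 12.6% | 9.6% | 7.2% |
| 22 | 0.02 | 7.3% | 6.3% | 5.9% | 5.5% | 5.4% |
| 22 | 0.05 | 10.6% | 8.7% | 7.4% | 6.3% | 5.9% |
| 22 | 0.10 | 17.2% | 12.4% | 10.1% | 7.7% | 6.4% |

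Repeat runs differ by up to about one percentage point. With one patient per provider the rate stays at 5%.

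**4. By contrast** (30 per arm, 2 to 6 providers):
- Unadjusted HT versus MBSR behaves like the omnibus test.
- Unadjusted HT versus FBT, with one clustered arm, rejects in 6–9% at ICC 0.05 and 7–14% at ICC 0.10.

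**5. Through the planned sequence.** The plan's procedure is "analyzed with a repeated measures ANOVA followed by a post-hoc Tukey’s test to compare treatment means when there is a significant effect". With 30 per arm and no clustering, a false finding that HT beats at least one comparator occurs in about 1.6% of null trials. With 2 to 6 providers this becomes about 2.5–4.7% at ICC 0.05 and 3.4–8.6% at ICC 0.10. HT falsely beating both comparators rises from 0.1% to about 0.6% (2 providers, ICC 0.05) or 1.6% (2 providers, ICC 0.10).

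**6. Power at a true 5% level.** This uses the plan's effect (f = 0.2 at r = 0.5 equals f = 0.4 on the change score), placed in the HT arm only.

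| Patients per arm | No clustering | ICC 0.05, c = 2 to 6 | ICC 0.10, c = 2 to 6 |
|---|---|---|---|
| 22 | 82% | 68–78% | 57–74% |
| 30 | 93% | 78–89% | 65–84% |

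**The case against.** **The inputs are assumed.** The article gives no provider number, caseload or ICC. This stands: the size is conditional, and at ICC 0.02 the omnibus rate is only 6–8%. A reader might infer that the error rate simply exceeds twice 5%. The document does not support that as a general statement. With 30 per arm it needs roughly ICC 0.05 and 2 to 3 providers, or ICC 0.10 and up to about 4 to 5. With 22 completers per arm, 3 providers at ICC 0.05 give about 9%.

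**The omnibus rate is not the rate of false HT claims.** It also counts MBSR looking best or worst, and HT looking worse. This stands too: through F and then Tukey, false claims for HT remain below 10% in every setting examined, although they rise several-fold in the worst ones.

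**The Introduction does not describe this problem.** It says that "the therapeutic relationship is the most important factor for therapeutic success", and a reader might infer that this predicts a large provider ICC, or that clustering is the very explanation the trial sets out to exclude. Neither follows. The argument there concerns a more intense relationship in home-based care, which is a mean difference between settings. It says nothing about variation between individual providers, and a provider random effect would not address it. A relationship can also matter while varying mainly between patients of the same provider.

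**Manuals, podcasts, training and supervision limit provider variation.** That is plausible and argues for the lower ICCs, but does not make the ICC zero. FBT clinicians would not inflate the error in the same way if they work across arms; the article does not say whether they do.

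**A few providers cannot support a variance estimate, and such detail belongs in a fuller plan.** The first part stands and is why the clustered model is proposed beside the ANOVA. The second does not dispose of the point: the article itself fixes the primary model, sizes the trial on it and lists the factors for sensitivity analysis. That stated model does not fit the stated delivery.

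**Conclusion.** The point holds in conditional form. Add-on providers are nested in arm, and both the primary analysis and the sample size ignore this. If providers treat several patients each, the standard errors of the add-on contrasts are too small.

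The likely size runs from slight to material. Assuming 2 to 6 providers per add-on arm and ICCs of 0.02, 0.05 and 0.10, the omnibus test and the unadjusted HT versus MBSR contrast reject in about 6–8%, 7–13% and 9–22% of null trials with 30 per arm. With 22 completers per arm the ranges are about 6–7%, 6–11% and 8–17%. HT versus FBT is less affected. With about ten providers per arm and ICC up to 0.10, inflation is small. The direction is secure; the magnitude is not known from the document.

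**What to change.** 1. Record the add-on provider for each patient from the first enrolment. Without this field the correction may not be possible later.
2. Keep the repeated measures ANOVA and pre-specify beside it a partially nested mixed model. It should have a provider random effect on change in FBT-HT and FBT-MBSR, none in FBT, and Satterthwaite or Kenward–Roger degrees of freedom. Report the estimated ICC.
3. If providers are too few to estimate the variance, report the contrasts at fixed ICCs of 0.02, 0.05 and 0.10.
4. Report the number of providers and their caseloads. If superiority of FBT-HT does not survive this analysis, limit the conclusion to the providers studied.
5. State the power of the existing 90 patients under the same ICCs.

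The cost is one data field and one additional model. The downside is wider intervals and lower power for the add-on contrasts, as the last table in the working shows. Nothing in treatment delivery changes.

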#### Family-based treatment

FBT is a manualized three-phase intensive outpatient treatment, in which parents play an active and positive role in helping their child (1) reach the weight expected for their age and height, (2) regain control over their eating and (3) promote the child’s normal development through in-depth discussion of the critical developmental issues affecting their child. FBT will be conducted by state-certified psychotherapists in weekly sessions of 60 min together with the patient and the caregiver(s) in the facilities of the Clinic for Child and Adolescent Psychiatry. Siblings are not actively involved in treatment and will not be included in the evaluation. In the first phase, parents/caregivers are empowered to be responsible for the adolescent’s eating behaviors and weight by providing meal structure in addition to preparing and serving meals for the adolescent. Once weight is restored and a more conflict-free eating situation is achieved, phase two follows, in which control over eating is returned to the adolescent. Phase three aims to prevent relapse, but also to reintegrate the adolescent into a daily routine appropriate for their developmental age.

#### FBT: home treatment

FBT-HT is an adapted intervention that complements manualized outpatient FBT with HT. During the treatment period of 12 weeks, the HT professional is to visit the family twice a week for 60–90 min at home or, at the family’s request, another agreed upon location. The HT intervention starts with a diagnostic component undertaken to assess eating-disorder maintaining factors of the individual (e.g., body-checking, frequent self-weighing) and of family interactions (e.g., parental criticism, unhelpful family communication around meal-times). Subsequently, the individual HT goals are set by involving the patient and parent(s)/caregiver(s), as well as the FBT-therapist that collaborates with the HT professional. The intervention is then carried out through regular visits, during which the HT professional takes part in family meals. The HT professional addresses crucial issues regarding interactions between the patient and the parents and gives advice on how to overcome them. The main goal is to provide practical support to parents in refeeding their adolescent, the key task of the first phase of FBT. Another important part of the intervention is to foster the patients’ and families’ resilience factors and promote the patient’s resources in everyday social life (e.g., restart hobbies, meet friends). HT sessions require the participation of at least one parent/caregiver and can be administered in different settings involving the patient, siblings or other significant people in the family environment.

#### FBT: MBSR (control group)

During the 12-week treatment period, FBT-MBSR is to include two 30-min consultations per week to practice and implement mindfulness for patients. The MBSR interventions are manualized exercises and meditations based on the 8-week MBSR program described by Kabat-Zinn [21]. The exercises and meditations are adapted to the needs of adolescents and supplemented with practices from mindfulness exercises with children and adolescents in psychotherapy [13]. To not to deviate further from the 8-week program manual, MBSR sessions are not timed to coincide with HT sessions. To support standardization and daily practice, meditation podcasts are provided, each lasting between 6 and 13 min. The MBSR therapist makes home visits for sessions or offers online appointments upon request. Each session includes meditation, a mindfulness exercise and also an opportunity to share and receive answers to possible questions.

### Measures

Demographic data as well as previous or current psychiatric treatment data will be collected from patients/their parent(s)/caregiver(s). During registration by telephone, patients are to be asked about the required language skills. All measurement instruments (see Table 1) are already digitized and to be electronically transmitted for the study via REDCap, a secure web-based electronic data collection application. The digitized version of the Eating Disorder Examination (EDE) [7] was previously investigated for equivalence with the original face-to-face EDE interview by our group; this study indicated that both instrument versions are overall equivalent in their measured scales, additionally showing that, as a diagnostic tool, the online version is generally answered more honestly [3].

**Table 1 Tab1:** Summary of measures

Construct	Measure	Respondent/format	Time point		
			Week 0	Week 12	12 months
Descriptives	Age, gender, comorbid diagnosis, menstrual status, driven sporting activities, premorbid BMI, medical history	A, C	×		
Primary outcomes	EDE	A_os_	×	×	×
	EDI-2	A_os_	×	×	×
	BMI	A	×	×	×
Secondary outcomes					
Health-related quality of life	KID SCREEN-27	A_os_	×	×	×
Vital parameters	Blood pressure and pulse	A	×	×	×
Expressed emotion	BDSEE	A_os_	×	×	×
Stress perception	PSS-10	C_os_	×	×	×
Mediator/moderator					
Family functions	FB-K	A_o_, C_o_	×	×	×
Exploratory outcome					
Child behavior	CBCL	C_oa_	×	×	×
Implementation characteristics					
Therapy evaluation	FBB	A_o_, C_o_		×	
Process analysis of methods	BPT	A, C, T	Weekly		

*A* adolescent, *C* caregiver, *T* therapist, *o* online, *os* online self-reporting, *oa* caregiver online reporting on adolescent, *BDSEE* Brief Dyadic Scale of Expressed Emotion, *BMI* body mass index, *BPT* Berner Patienten- Therapeutenstundenbogen, *CBCL* child behavior checklist, *ED* eating disorder, *EDE* eating disorder examination, *EDI-2* eating disorder inventory, *FB-K* family questionnaire, *FBB* treatment satisfaction (in German: Fragebogen zur Beurteilung der Behandlung), *PSS* Perceived Stress Scale

#### Implementation

The feasibility and acceptance of FBT-HT have already been demonstrated in our preceding pilot project [9], which also indicated the rates at which families eligible for this designed study are referred to our eating disorder unit. The quality analysis of FBT will be carried out in all three groups in weekly surveys using the Berner Patienten- und Therapeutenstundenbogen (BPT, English translation, The Bern Post Session Report) [22], an instrument developed in Switzerland to measure the quality of psychotherapeutic treatments. The questionnaires, independently completed by the patients and the therapists, will be matched after each session for the purpose of process analysis. The acceptability in terms of treatment satisfaction will be assessed by the FBB‐HT, which is an adapted version of the Fragebogen zur Beurteilung der Behandlung (FBB, English translation, The Questionnaire of Treatment Assessment) [27]. The FBB is rated on a five‐point Likert scale and administered at the 3-month follow-up assessment.

